#### The cognitive side-effects of ECT are correlated with treatment-related increases in gray matter

We will investigate the biological mechanisms behind the ECT/TMS response (and side effects) through a combination of imaging, epigenetics, genetics, and proteomics in the framework of the disrupt, potentiate, and rewire (DPR) hypothesis [30]. The mechanisms of ECT are to be understood as a sequence of events where neuronal circuits are disrupted, potentiated, and ultimately rewired. For the TMS patient group, we do not expect the same extent of the disruptive effects but will investigate changes that can explain the efficacy in terms of potentiation and rewiring. The TMS group will also provide a possibility of comparing treatment-related effects across treatment modalities.

### Research questions

In addition to the two primary hypotheses, several analyses can be performed that can shed light on the mechanisms of action suggested by the DPR hypothesis.

#### Neuroimaging

We predict that neuroimaging results in general will be in line with the DPR hypothesis: Disruption will mainly be seen at TP2 and TP3, to a lesser degree at time TP4 and will not be evident at TP5 (Table 1). Signs of potentiation are expected at TP3 and TP4, and rewiring is expected mainly at TP5 (some at TP4). Volume changes at TP3 and TP4 are expected to relate to side effects. We expect some signs of edema indicative of immediate disruption at two hours after the first ECT session, as measured by advanced DWI. Changes in diffusion properties at TP3 and TP4 will reflect potentiation, and changes at follow-up TP5 will reflect rewiring compared to baseline. Resting-state fMRI at follow-up will show connectome stabilization differing from baseline but will be disrupted after the 1st and 6th ECT session.

Based on previous proton magnetic resonance spectroscopy (^1^H-MRS) investigations in ECT, summarized in Erchinger et al. [100], we propose that N-acetylaspartate (a proposed marker of neuronal integrity), will temporarily decrease after ECT, reflecting the disruption in the DPR hypothesis. We also hypothesize that depressed patients will display lower glutamate levels at baseline compared to controls [101] and that an increase in glutamate levels from baseline to after treatment will be associated with positive treatment outcomes for both TMS [102] and ECT patients [103–107].

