### Electroconvulsive therapy (ECT)

*ECT* is a medical treatment in which electric currents delivered through scalp electrodes are used to intentionally trigger a brief seizure. Patients are under general anesthesia and muscular blockade during treatment sessions, which are provided two or three days per week for two to four weeks. ECT has remained the most effective acute treatment for major depressive episodes [14, 15] over the past 80 years. Even for patients with treatment-resistant, severe and sometimes life-threatening depressive episodes, the remission rates of ECT are up to 75% [16]. However, the use of ECT is still debated [17, 18], and the lack of an overarching model for the mechanism of action of ECT possibly contributes to its public controversy [19]. Considering the large number of people suffering from depression, the use of ECT is variable, with reported treated person rates (TPR; number of persons treated with ECT per 10,000 resident population per year) between 0.11 and 5.1 worldwide [20], possible due to worries about side effects.

ECT is associated with cognitive side effects [21, 22]. However, the literature is divergent and inconclusive regarding the nature and development of the neuropsychological profile of cognitive side effects [23, 24]. Most of the cognitive impairments seem to be limited to the first three days after ECT [25], and some patients even report an improvement in neurocognitive function [23]. While reduced autobiographical memory consistency has been well documented [26–28], a number of other cognitive functions has been shown to improve one month after ECT, compared with pre-ECT [24]. Although several guidelines highlight the importance of assessing cognitive function during ECT, there is no consensus regarding the optimal test battery and study design [24, 29], thus large well-designed studies investigating broad measures of cognition pre-post ECT are warranted.

There is substantial evidence for ECT-induced volumetric changes in brain gray matter areas [30, 31], which depend on electrode placement [32] and correlate with the electrical field strength [33]. Although there are conflicting results regarding the clinical relevance of these changes, some association with clinical response has been found [34, 35], and side effects may relate to hippocampal volume change [36, 37].

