**Fig. 1 Fig1:**
[figure not shown]
Study flow-chart. Assessments are performed at multiple time points before, during and after treatment as illustrated. CA, Core Assessment (includes neurocognitive tests, actigraphy and for the patient groups clinical assessment)

MRI, blood samples, neuropsychological assessments (including spatial navigation – a function residing in the hippocampus), clinical scales and depression scores from 100 patients in a major depressive episode will be collected. The ECT (*N* = 50) and TMS (*N* = 50) study groups will be followed over 5 time points (TP): baseline (TP1), during (after 1^st^ (TP2) and 6^th^ ECT or 10^th^ TMS (TP3)), after treatment series (TP4), and at 6 months follow-up (TP5). Healthy controls (*N* = 50) will be assessed at four time points (corresponding to TP1, TP2, TP4 and TP5 to estimate variance due to noise, and to control for effects of time. There are comprehensive and in-depth assessments of participants, spanning from diagnosis, history and imaging to neuropsychological profiling, blood biomarkers, genetics, and epigenetics (see Fig. 1 and Table 1).

**Table 1 Tab1:** Variable overview

	Timepoints (TP) for analyses	TP1		TP2	TP3	TP4	TP5
	Timepoints relative to treatment	Baseline, before treatment		During treatment		After treatment	
	Timeframe for each test	< 7 d of first ECT/TMS	1–2 h before first ECT/TMS	1–2 h after first ECT/TMS	before 7th ECT/11th TMS	7–14 d after last ECT/TMS	6 mo after ECT/TMS series
Clinical assessments ^c^	Clinical examination	x					
ECT- stimulus specific measures ^b^	EEG, pulse width, charge, amplitude, frequency, pulse train duration, seizure duration, electrode placement and reorientation time		x		x		
	Current and concomitant medication	x			x	x	x
Symptom severity ^c^	MADRS [47]	x			x	x	x
	BDI [48]	x			x	x	x
	CGI [49]	x			x	x	x
	EMQ [50]	x			x	x	x
	MMSE [51]						
Radiology	MRI: T1, T2, MRS, ASL, DWI, rsfMRI		x	x	x	x	x
Neurocognitive assessments aligned with GEMRIC recommendation	1. RAVLT [52, 53]	x				x	x
	2. Phonemic Fluency [54]	x				x	x
	3. Semantic Fluency [54]	x				x	x
	4. SDMT [55]	x				x	x
	5. TMT A + B [54]	x				x	x
	7. DSB [55]	x				x	x
	8. AMT [56]	x				x	x
	9. MoCa version 7.1 [57]	x				x	x
	10. NART [58]	x				x	x
	11. QIDS-SR 16 [59]	x				x	x
Study specific neurocognitive assessments	1.VAMS^a^,^c^ [60]	x				x	x
	3. Spatial navigation: Memory retrieval task [61, 62], Four Mountain [63], Sea Hero [64]	x				x	x
	4. RCFT [65]	x				x	x
	5. CWIT [54]	x				x	x

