#### Anesthesia

The anesthetic agent used for induction to ECT will be either propofol, etomidate or thiopental, as decided by the anesthesiologist. All patients are preoxygenated one to two minutes before treatment with oxygen-enriched air. All patients will also receive the muscle relaxant suxamethonium about 90 s before the stimulus is given. Hyperventilation should be maintained during this period even with high oxygen saturation. The use of other medication deemed necessary during anesthesia will be decided by the anesthesiologist.

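### Changes at the TP2 scan cannot be credited to ECT-specific disruption, because only ECT patients have been anesthetized shortly before it

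*Protocol article*

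**What the plan says.** All from the protocol article.

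- **Timing.** Table 1 schedules the full MRI set (T1, T2, MRS, ASL, DWI, rsfMRI) shortly before the first session and again "1–2 h after first ECT/TMS" (TP2). TP3 is "before 7th ECT/11th TMS".
- **Interpretation.** Under Neuroimaging: "Disruption will mainly be seen at TP2 and TP3, to a lesser degree at time TP4 and will not be evident at TP5". For DWI: "We expect some signs of edema indicative of immediate disruption at two hours after the first ECT session, as measured by advanced DWI". Resting-state fMRI "will be disrupted after the 1st and 6th ECT session". The same section assigns diffusion changes at TP3 and TP4 to potentiation.
- **Anesthesia.** Under Electroconvulsive therapy (ECT): "Patients are under general anesthesia and muscular blockade during treatment sessions". Under Anesthesia: "The anesthetic agent used for induction to ECT will be either propofol, etomidate or thiopental, as decided by the anesthesiologist". All ECT patients also receive preoxygenation and suxamethonium, with hyperventilation maintained up to the stimulus.
- **Comparators.** The TMS section describes no anesthesia, and healthy controls are untreated. Under Study design, controls are scanned at TP1, TP2, TP4 and TP5 to gauge noise and the passage of time. Under Hypotheses, the TMS group offers a comparison across modalities: "For the TMS patient group, we do not expect the same extent of the disruptive effects".
- **Recording.** Clinical assessments lists the induction agent, charge, seizure duration and reorientation time. It does not list agent dose or the time from induction to scan.

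**The concern.** An ECT session contains at least two things that could alter a brain scan one to two hours later: the stimulus with its seizure, and the anesthetic procedure around it. The article assigns the TP2 change to disruption, a step in a proposed mechanism of ECT, and elsewhere contrasts ECT as disruptive with TMS as nondisruptive. Neither comparison group had an anesthetic, so neither shows what the scan would look like after anesthesia alone. The pre-session scan does not help either, since it precedes induction.

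At stake is what the study may conclude from its only scan scheduled within hours of a session. A TP1-to-TP2 change found in ECT patients and absent in the others would fit ECT-specific disruption, an anesthetic effect, or a mixture of the two.

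**Working it through.** The plan states no figure for this question. Its sample sizes (14 per group, 22 paired) concern cerebral blood flow. The check is whether the two effects can be estimated separately.

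**Inputs.** 50 ECT, 50 TMS and 50 control participants (Abstract, Methods). Anesthesia before TP2: all ECT patients, nobody else (Electroconvulsive therapy, Anesthesia, TMS and Study design sections).

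**Step 1: expected change from TP1 to TP2.** Let t be time and noise, s the stimulus and seizure, a the anesthetic procedure and m a TMS session. Assume the effects add and t is common to all groups, which favors the plan.

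| Group | Expected change |
|---|---|
| ECT | t + s + a |
| TMS | t + m |
| Controls | t |

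ECT minus controls = s + a. ECT minus TMS = s + a − m. Only the sum s + a ever appears. The pairs (s = x, a = 0) and (s = 0, a = x) predict the same data for any x.

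**Step 2: rank of the design matrix, 150 rows.**

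- Intercept, ECT, TMS: 3 columns, rank 3.
- Add an indicator for anesthesia before TP2: 4 columns, rank 3. Its correlation with the ECT indicator is 1.0.
- Use three agent indicators instead: 6 columns, rank 5. They sum to the ECT column, so agents can be compared within ECT, but their shared effect stays merged with ECT.

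**Step 3: illustration of consequence.** Suppose s = 0 and m = 0, all 50 per group are scanned, and anesthesia alone shifts the change score by d standard deviations in either direction. For a two-sided 5% test of ECT against TMS, the probability of a significant result in the direction of the shift is

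Φ(d·√(50/2) − 1.96) = Φ(5d − 1.96)

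| Assumed d | 5d − 1.96 | Probability |
|---|---|---|
| 0.2 | −0.96 | 17% |
| 0.3 | −0.46 | 32% |
| 0.5 | 0.54 | 71% |
| 0.8 | 2.04 | 98% |

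It reaches 80% at d = (1.96 + 0.84) × √(2/50) = 0.56. Every d here is assumed; the documents give none.

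**Step 4: what TP3 can add.** The article places TP3 after the 6th and before the 7th ECT, so the scan need not fall on an anesthetic day, but nothing rules that out. For resting-state fMRI, disruption is already predicted after the 6th ECT, so TP3 can lend support. For DWI it cannot, because the article assigns TP3 diffusion changes to potentiation. Healthy controls have no TP3 assessment, so only TMS patients are available for comparison there.

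**The case against.** The strongest reply is that anesthesia is part of ECT as given. The article says so, and an effect of the ECT session can fairly be read as an effect of the whole procedure. The study is observational and declared exploratory, so an anesthesia-only or sham group was never in scope. The induction agent is already recorded. All of this stands. It supports describing the TP2 change as a whole-session effect; it does not support assigning that change to disruption as an ECT mechanism.

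A reader might be tempted further than the documents allow:

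- **That the article claims a seizure-induced change.** It does not use that term. It speaks of immediate disruption after the first session.
- **That the results are biased toward the prediction.** Nothing in the documents says an induction agent produces edema or any other DWI change at this interval, or in which direction. Non-identifiability is shown; directional bias is not.
- **That a TP2 test of ECT against TMS is fixed.** The TP2 predictions name ECT sessions, and the sentence on TMS names no time point or imaging measure. The point is that no such contrast could settle the question if it were made.
- **That TP2 is the main test of disruption.** TP3 is named alongside it.

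Leaving covariates to a fuller analysis plan is normal, but no analysis plan can supply a contrast the design lacks, and the interpretation is stated in the article itself.

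**Conclusion.** The point holds for the TP2 scan. Exposure to anesthesia is complete in one group and absent in the other two, so ECT-specific disruption and the anesthetic procedure cannot be separated there, by between-group comparison or by covariate adjustment. The size and sign of any anesthetic contribution are unknown from the documents.

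The reach is limited. This is a research question beyond the two primary hypotheses. Of those, one uses baseline cerebral blood flow and the other treatment-related gray-matter increases, with volume predictions at TP3 and TP4; neither depends on TP2. TP4, at 7–14 days after the last session, is much less exposed. The conclusion rests on every ECT patient being anesthetized and on no TMS patient or control being so, both as the article describes.

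**What to change.** 1. **Wording (Neuroimaging).** Describe TP1-to-TP2 changes as the effect of the ECT session including anesthesia. State that they will not be attributed to ECT-specific disruption on the TP2 change or a TP2 group contrast alone.
2. **Supportive model within ECT.** Regress the TP1-to-TP2 change on seizure duration and charge, adjusted for age, induction agent, agent dose and minutes from induction to scan. Age is needed because the initial stimulus dose is age-based. First-session charge may therefore carry little information beyond age, and its coefficient may be imprecise. Do not treat reorientation time as seizure-specific, since it follows the same anesthetic. Agent and stimulus are not randomized, so label the model supportive and not decisive.
3. **Data.** Take agent dose and induction-to-scan time from the anesthesia record. At submission 11 of 50 ECT patients were included, leaving 50 − 11 = 39 for prospective capture.
4. **Use of TP3.** For resting-state fMRI, cite TP3 as supporting evidence only if that scan was not on the day of an anesthetic. Do not require a DWI change to persist to TP3: that would conflict with the article's own reading of TP3 diffusion and would reject a genuinely brief edema.

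**Cost.** A few sentences, two extra fields and one model, with no added scans or visits and no change in care. The price is that TP2 alone no longer supports a claim of ECT-specific disruption.

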#### Clinical outcomes

Both ECT and TMS will reduce MADRS scores at TP4, and we expect ECT to be more efficient with a higher proportion of responders and remitters compared to TMS. In patients treated with ECT, we hypothesize a symptom fluctuation following the trajectory of the disruption and symptom load curves [30].

#### Neuropsychological outcomes

We expect group differences between depressed patients and controls at baseline explained by the “state”, “scar”, and "trait" hypotheses [11]. We expect processing speed and attention to improve following remission of depressive symptoms, explained by the “state” hypothesis. Further we expect executive functions to remain relatively stable, as suggested by the “trait” and “scar hypotheses” [11, 108].

Cognitive side effects seen with ECT (disruptive treatment) are not expected to be seen with TMS (nondisruptive treatment). The cognitive tests of spatial navigation will be used to assess specific hippocampal functions, and we expect the results to be in line with the DPR hypothesis, hence a reduction in performance after end treatment (TP4) and normalization at TP5. Moreover, we expect the hippocampal volume change to correlate with a reduction in performance. Reduced spatial navigation performance will also correlate with increased cortical thickness (broadly distributed volume change) for ECT patients. However, improvements relative to baseline are expected (TP5) for hippocampal functions, i.e. functions that are impaired from a “scar perspective”, such as category fluency, memory and language, in line with the concept of the DPR model. Finally, existing differences between the TMS and ECT groups pre- treatment could elucidate on the cognitive profile in treatment resistant MDD and could be explored.

#### Activity monitoring

Patients are expected to show increased daytime activity, decreased variability in activity levels, decreased nighttime activity and improved quality of sleep after ECT treatment [109, 110]. Motor activity will be assessed by both linear and nonlinear analyses of variability and complexity [111]. Furthermore, stabilization of the circadian rhythmicity should be observable in motor activity, as well as in the peripheral body temperature [90, 112]. Sympathetic activation will fluctuate (disrupt and potentiate); however, it will subsequently decrease, alongside an increase in para-sympathetic activation after ECT, observable in digital biomarkers (heart rate, heart rate variability and electrodermal measures) [88]. Finally, a machine learning-based multisensory approach, combining the digital biomarkers and motor activity recordings of Empatica E4, could be an interesting alternative method for analyzing these data [113].

#### Blood biomarkers

Several treatment-response predictors for MDD have been proposed in recent years, but there are currently no blood-based disease progression or therapy-response biomarkers in clinical use [114]. We aim to advance our understanding of the molecular mechanisms underlying both the pathogenesis of severe MDD and the treatment response to ECT by using a multiomics approach on patient blood and serum samples. By using proteomics, genomics, transcriptomics, and epigenetics to generate multiomics profiles of individual patients we hope to identify biological predictors of treatment outcome that can help guiding personalized, interventional strategies.

Previous research has indicated that depression is accompanied by increased levels of inflammatory markers, such as C-reactive protein (CRP) and interleukin-6 [115], which could be particularly relevant for treatment-resistant depression [116]. It has also been suggested that acute ECT sessions transiently increase inflammation, while full treatment series may reduce inflammation [117]. To elucidate the effect of ECT on neuroinflammatory markers and other relevant blood biomarkers, blood samples will be collected at all timepoints. We expect increased levels of neuroinflammatory markers immediately after treatment and in the short term but not at TP4 and TP5 [117].

Large collaborative studies, including the psychiatric genomics consortium (PGC), have recently identified many common genetic risk variants and rare copy number variants in MDD [118]. Treatment-resistant, severe depression is a clinical subgroup that may have a distinct genetic risk profile [119]. We hypothesize that a joint analysis of patients recruited for ECT treatment across the PGC sites will reveal common and rare genetic risk variants. Moreover, we hypothesize that it will also be possible to detect genetic markers of treatment response using this collaborative framework. Clinical data, and data from genome-wide genotyping will be analyzed locally, also shared, and meta-analyzed within international consortia, such as GenECT-ic [94].

Epigenetic markers will be investigated, both to find markers to predict treatment response and markers that change during the treatment.

We expect changes specific to ECT and will test hypotheses from published reports as well as investigate effects related to Brain-Derived Neurotrophic Factor activation, markers of neurogenesis and immunoactivity. As described previously [120], we aim to supplement the measurements of peripheral biomarker levels by peripheral blood messenger ribonucleic acid (mRNA) levels (array-based genome-wide DNA genotyping, methylation profiling of target genes and real-time reverse transcription polymerase chain reaction mRNA measurements) and genome-wide methylation studies.

In summary, the study will provide a comprehensive dataset, that will be used for specific hypothesis testing and explorative investigations to improve our understanding of depression and neurostimulation treatments. The putative biomarkers will be evaluated for inclusion in a future algorithm for the outcome expectancy score. Such a tool could be used for clinical decision support and would provide patients with evidence-based likelihood estimates for clinical outcomes and provide opportunities for more personalized treatment choices.

## Data Availability

All data and blood will be handled according to approvals (ethical committee and data protection authorities) and research regulations at the Haukeland University Hospital (HUH) and at University of Bergen (UiB). Data will be collected and stored on a research server hosted by the IT-department at HUH and at the research server at UiB. Data will be shared with GEMRIC through a secure research server (SAFE) located at the University of Bergen. The dataset for this study is not publicly available due to Norwegian laws and regulations for medical research (Act on Medical and Health Research, General Data Protection Regulation (GDPR) and The Personal Information Act with regulations).

## ﻿Abbreviations

ABCD: Adolescent Brain Cognitive Development—study
AMT: Autobiographical Memory Test
ASL: Arterial Spin Labeling
BDD: Bipolar depressive disorder
BDI: Beck Inventory test
BL: Bilateral
CBF: Cerebral blood flow
CGI: Clinical Global Impression Scale
CRP: C-reactive protein
CWIT: Color word interference test
DLPFC: Dorsolateral prefrontal cortex
DPR: Disrupt, potentiate and rewire
DWI: Diffusion weighted imaging
ECCA: Electroconvulsive Cognitive Assessment
ECT: Electroconvulsive therapy
EDTA: Ethylenediaminetetraacetic acid (edetic acid)
EEG: Electroencephalography
EMQ: Everyday Memory Questionary
EPI: Echo planar imaging
FA: Flip angel
GEMRIC: The Global ECT-MRI Research Collaboration
HUH: Haukeland University Hospital
MADRS: Montgomery and Aasberg Depression Rating Scale
MDD: Major depressive disorder
MMSE: Mini Mental Status
MRI: Magnetic resonance imaging
mRNA: Messenger ribonucleic acid
MRS: Magnetic resonance spectroscopy
NART: National Adult Reading Test
NOK: Norwegian kroner (currency)
PAX-gen tube: Collection of blood for stabilization of intracellular RNA
PDQ-D 5- item: Perceived Deficit Questionary – Depression 5-item
PPG: Photoplethysmography
QIDS-SR: Quick Inventory of Depressive Symptomatology – Self-Report
RAVLT: Rey Auditory Verbal Learning Test
RCFT: Rey – Osterrieth Complex Figure Test
rsfMRI: Resting State Magnetic Resonance Imaging
RUL: Right unilateral
SDMT: Symbol Digit Modality test
TA: Time of acquisition
TE: Echo time
TMS: Transcranial magnetic stimulation
TMT: Trail Making Test
TP: Time point
TPR: Number of persons treated with ECT per 10.000 resident population per year
TR: Repetition time
UiB: University of Bergen
VAMS: Visual Analog Mood Scale
